### Primary outcome measure

#### Work-related rumination

Work-related rumination is measured using the cognitive irritation subscale of the Irritation Scale (IS) [76]. This subscale consists of three items, each with a 7-point Likert response scale (range 0–6) to assess workers’ ability to mentally detach from work during leisure time. The level of internal consistency previously reported was Cronbach’s *α* = 0.89 [76].

### Secondary outcome measures

All secondary outcomes are health-related.

### Mental health

#### Depression

Symptoms of depression is assessed with the Patient Health Questionnaire (PHQ-8) [88]. This instrument consists of eight items. Participants indicate how “down, depressed, or hopeless” they feel on a 4-point Likert response scale (range 0–3). Internal consistency has been reported as *α* = 0.84 [89].

#### Insomnia severity

Insomnia severity is assessed using four items from the Insomnia Severity Index (ISI) [90]. For example, participants are asked to rate, on a 5-point Likert scale (range 0–4), how much they struggled to sleep during the night. A summation score from participant’s answers is calculated. ﻿Internal consistency of this measure has been found to be *α* = 0.74 [90].

### Work-related health

#### Emotional exhaustion

Emotional exhaustion is being measured with the Maslach Burnout Inventory General Survey (MBI-GS-D). Five items from the exhaustion subscale, assessed on a 6-point Likert scale (range 0–6), are used. Participants rate statements indicating whether their work made them feel emotionally drained or exhausted. The internal consistency of this measure has been reported as *α* = 0.85 [91].

#### Thinking about work

Further aspects related to thinking about work are assessed using the work-related rumination questionnaire (WRRQ) [92]. The subscale, affective rumination, consists of five items and assesses workers’ negative and reoccurring thoughts about work; for example, “﻿do I feel irritated by work issues when not at work?” The second subscale, problem-solving pondering, also consists of five items and assesses workers constructive thoughts about how they can improve their performance; for example, “after work, I tend to think of how I can improve my work-related performance”. All items are rated on a 7-point Likert response scale (range 0–6). Internal consistency has been found to be *α* = 0.90 for affective rumination and *α* = 0.81 for problem-solving pondering [93].

#### Recovery experiences

Participants’ recovery experiences are measured employing the DRAMMA questionnaire (DRAMMA-Q), which consists of six subscales measuring detachment, relaxation, autonomy, mastery, meaning and affiliation. All 18 items are rated on a 5-point Likert scale (range 0–4). DRAMMA-Q was based on existing, validated questionnaires, and has itself been validated [94].

### Other variables

The following measures are not directly related to mental health.

### Work characteristics

Various work characteristics of participants are also assessed. Unless otherwise stated, questions refer to the past 7 days. Work engagement is assessed using the Utrecht Work Engagement Scale (on a scale 1–7) (UWES: [95]). Other aspects such as, vitality (PANAS: [96, 97]) (on a scale 1–7), perceived need of recovery (NFR: [98]) (on a scale 1–5), and objective (TTCT) and subjective creativity (on scales 1–5) [99–101] are also assessed. Further measures include the perceived number of unfinished tasks (on a scale 1–5) [102]; work performance (e.g., did participants accomplish tasks that were beyond their job description?) (on a scale 1–7) (OCB: [103]); and whether participants experienced time pressure (on a scale 1–5) (ISTA: [104]. We also take into consideration whether participants experience autonomy in the order in which they completed their tasks, as well as the variety of tasks at hand (on a scale 1–5) (WDQ: [105]), and whether they perceive receiving social support from their colleagues (on a scale 1–5) (SzSU: [106]).

### Personal characteristics

For assessing workers ability to manage boundaries between their work and private life, we employ the Work-life Indicator (WLI) [107] and Work-Life-Balance scale (on a scale 1–6) (TKS-WLB: [108]) (on a scale 1–6), as well as the Life Satisfaction Scale (on a scale 1–7) (SWLS: [109]). Participants perceived levels of physical health and subjective wellbeing are measured (see for instance, [46]). Personal characteristics include resilience (RS) (on a scale 1–5) [110].

### Potential mediator, moderator

#### Mediator

##### Health behaviour: Recreational activities.

The frequency of participants’ engagement in recreational activities after work during the past week is assessed using 21 items from the Recreation Experience and Activity Questionnaire (ReaQ) [111]. Items are rated on a 5-point Likert scale (range 0–4) and have an internal consistency of ﻿*α* = 0.88 [61].

#### Moderator

##### Technical aspects: User experience.

Participants’ digital experiences using Holidaily are assessed employing a 28-item questionnaire from the AttrakDiff2 [112]. A seven-point Likert scale is used for responses. The questionnaire provides information concerning global attractiveness (ATT), pragmatic quality (PQ), hedonic quality-identity (HQ-I), and hedonic quality-stimulation (HQ-S), and has an internal consistency of ﻿*α* = 0.94 [58].

### Statistical analyses

﻿All analyses will be reported according to the Consolidated Standards of Reporting Trials (CONSORT) for web-based and mobile health interventions [113], employing intention-to-treat (ITT) procedures*.* All reported *p* values will be two-tailed, with α = 0.05 the chosen significance level. Characteristics of the sample will be analysed using descriptive statistics. For the primary and all continuous secondary outcomes, Cohen’s *d* will be calculated based on group differences in means post-vacation, standardized by the pooled standard deviation of the post-vacation scores. Missing data will be dealt with following the recommendations of Little and Rubin [114] and Schafer [115]. Multiple imputation (MI) is an especially robust approach for handling missing data [116]. A stability score, in form of correlation analyses, will also be reported in the results section.

### Primary analysis

The primary analysis will evaluate the efficacy of Holidaily. The primary endpoint is the difference in work-related rumination, assessed using the irritation score, between the IG and CG 2 weeks after the vacation. We will use analysis of covariance (ANCOVA) to investigate differences in the primary outcome between the two groups, as simulation studies have demonstrated that ANCOVA is the most robust method for analysing RCT’s, in terms of protecting against bias, while enhancing precision and statistical power [117, 118]. Baseline scores for the primary outcome will be included as a covariate. In addition, for the analyses of differences in work-related rumination at the end of the last work day, mid-vacation and at the end of the first work day Bonferroni-Holm corrections will be used to reduce the chances of chance capitalisation [119].

### Sensitivity analyses

To assess the robustness of these results, sensitivity analyses will be conducted. First, a separate analysis will be performed for participants who complete the main assessment 2 weeks after vacation (study completer sample). Second, all participants that used the app at least three times per week will be analysed (per protocol sample). Third, to account for potential baseline differences, despite randomisation, we will include all continuous variables with a between group difference of *d* = 0.20 or more and each categorical variable with 10% difference or more as covariates.

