## Methods

### Study design

For a proof of concept study and employing a pre-post-design, our research team has investigated the feasibility of use of the app-based intervention “Holidaily 1.0.” amongst workers (*N* = 77) [58]. Holidaily is a low-intensity, gamified, smartphone-based intervention. The app provides users with three suggestions promoting recovery behaviour daily. In this study, the intervention was begun 2 weeks prior to each worker’s vacation and continued beyond their return to daily working life. Initial findings were promising, as workers reported a significant improvement from 2 weeks before to 2 weeks after their vacation, and exhibited reduced work-related rumination during their leisure time, with an effect size of *d* = 0.68. To date, research indicates that, with no intervention, mental health variables resume baseline scores within 2 weeks after a vacation has ended [47]. Our next step is to establish whether meaningful effects can also be detected when an intervention and control group are compared.

Therefore, the current two-armed randomised controlled trial is being conducted to evaluate the efficacy of the app-based intervention “Holidaily 2.0” relative to a waitlist-control group (CG). All participants are invited via email to complete online questionnaires 2 weeks prior to their vacation, on their last working day, in the middle of their vacation, at the end of their first day working post-vacation, and 2 weeks after their vacation has ended (see Table 1). The intervention group receives an additional questionnaire 4 weeks after their vacation (extended follow-up). On average, these assessments last 15–30 min each. After the CG complete their final questionnaire, 2 weeks after their vacation, they receive an automated code via Email which allows them to immediately access Holidaily.

**Table 1 Tab1:** Overview of variables and measuring time points

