#### Assessment and allocation to the intervention

Participants are randomised to the conditions through a computer-generated algorithm created by Unipark. The allocation sequence is concealed to the researchers until interventions are assigned. For each measurement timepoint, participants receive an individual link via email that invites them to complete the online questionnaires at Unipark. Participants in the intervention group receive a personalized reminder 2 weeks after their vacation via email, asking them to complete the final questionnaire. All study-related information will be stored securely at the study site and handled with great care. Data are recorded and evaluated pseudonymised and transmitted in encrypted form. Data are stored on the server of Leuphana University in Lueneburg. Neither personal photos nor the content of notes in the app is transmitted or analysed. Only the amount of Dailys will be recorded for each participant.

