#### Waitlist-control group

Participants in the waitlist-control group (CG) are invited to answer the same questionnaires following the same timeframe as the IG. However, subjects in the CG only receives access to Holidaily 2 weeks after they have returned to work. Controls can, therefore, use Holidaily during their subsequent daily working life and next vacation.

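### The per-protocol sample is defined by app use that no control can have before the primary assessment, so it cannot check the robustness of the randomised comparison

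*Protocol article*

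**What the plan says.** The Primary analysis section sets the endpoint as the difference in work-related rumination "between the IG and CG 2 weeks after the vacation". It is analysed by ANCOVA, and "Baseline scores for the primary outcome will be included as a covariate". The Statistical analyses section places the reporting under intention to treat ("employing intention-to-treat (ITT) procedures").

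The Sensitivity analyses section opens with the purpose: "To assess the robustness of these results, sensitivity analyses will be conducted". It then lists three analyses: completers of the T5 assessment, the per-protocol sample, and adjustment for baseline imbalances. The only rule for the second is that "all participants that used the app at least three times per week will be analysed (per protocol sample". It gives no criterion for controls, no comparator, no weeks over which use is counted, and no adjustment for selection on use.

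On control access, the Waitlist-control group section says that "subjects in the CG only receives access to Holidaily 2 weeks after they have returned to work". The Study design section fixes the order of events: "After the CG complete their final questionnaire, 2 weeks after their vacation, they receive an automated code via Email".

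On usage data, the section on assessment and allocation says: "Only the amount of Dailys will be recorded for each participant". The section on secondary outcomes and other variables says instead that compliance will be tracked as how often the app was used.

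**The concern.** A sensitivity analysis of a randomised contrast should keep that contrast and vary an assumption behind it. Here the membership rule depends on something that only one arm can do before the endpoint is measured. Either there is no comparison, or the comparison is between volunteers for frequent use and an unselected control arm.

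Frequent users may differ from infrequent users in motivation, workload or strain whether or not the app works. The protocol itself expects use to be non-random. Its background and explorative hypotheses link user experience to engagement and engagement to efficacy, and its limitations expect work stress after the vacation to lower motivation and raise the effort of recovery behaviour. Adjusting for baseline rumination does not remove differences in factors that were not measured or not modelled.

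The interpretation of the primary result is at stake. Agreement between the two analyses would be reported as robustness although selection alone could produce it. Disagreement would be just as hard to read. With a design effect of only d = 0.20, even modest selection is of comparable size.

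**Working it through.** **Step 1: the plan's own figure.** Inputs from the Sample size calculation section: d = 0.20, two-sided 5% level, 80% power; allocation is 1:1. The two-sample t-test (noncentral t) needs 393.4 per arm, so 394 per arm and 2 × 394 = 788. This matches the stated N, with power 80.06%. The normal approximation gives 393 per arm, 786 in total.

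**Step 2: controls in the sample as written.** Membership needs app use at least three times per week. Controls receive their access code only after the T5 questionnaire, and T5 is the primary endpoint. Controls eligible by T5: 0 of about 394. No between-group difference can be estimated.

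**Step 3: users against all controls.** The plan does not state this reading, but it is the natural way to recover a comparison. Let a be the adherent share of the intervention group. Let g be the gap, in SD, by which adherers would have scored lower than non-adherers without the app. Under a true null, adherers score g below non-adherers. By randomisation, controls contain the same mix of would-be adherers (share a) and non-adherers (share 1 − a). So

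spurious difference = g − a × g = (1 − a) × g.

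The documents give neither a nor g. Assumptions: a from 0.30 to 0.70 and g from 0.2 to 0.5 SD, with g taken as what remains after baseline adjustment, SD = 1, and no dropout. The standard error is √(1/(394a) + 1/394). The rejection rate is the two-sided 5% normal test shifted by bias/SE.

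| a | g | users | bias = (1 − a)g | SE | bias/SE | rejection under a true null |
|---|---|---|---|---|---|---|
| 0.70 | 0.2 | 275 | 0.30 × 0.2 = 0.06 | 0.0785 | 0.76 | about 12% |
| 0.50 | 0.3 | 197 | 0.50 × 0.3 = 0.15 | 0.0873 | 1.72 | about 40% |
| 0.30 | 0.5 | 118 | 0.70 × 0.5 = 0.35 | 0.1049 | 3.34 | about 92% |

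The middle case is 0.15/0.20 = 75% of the design effect.

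**Step 4: cross-check with a different model.** Take users as the top share a of a latent adherence score that correlates at r = 0.1 to 0.3 (assumed) with a better outcome. The spurious d is 0.05-0.15 at 70% use, 0.08-0.24 at 50% and 0.12-0.35 at 30%. The null is rejected in about 10% to 91% of trials. The two models give a similar range.

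**Step 5: direction.** If those with most need use the app most, g changes sign and the same magnitudes count against the app. In the middle case a true effect of 0.20 would appear as 0.20 − 0.15 = 0.05.

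**The case against.** The strongest reply is that this is one of three sensitivity analyses and that the confirmatory analysis is by intention to treat. The protocol's limitations section also reserves strong efficacy conclusions for the primary outcome. In a waitlist design a usage threshold would naturally restrict only the app arm, and a condensed article may leave the exact rule for controls to a fuller document. Selection is also a known limitation of any per-protocol analysis.

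The point about weight stands: nothing confirmatory changes. The point about missing detail does not remove the defect. The article states the population rule, and keeping all controls, the rule this reply supplies, gives exactly the one-arm selection in step 3. The stated purpose is robustness, which that comparison cannot show.

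Three stronger readings are tempting, and the documents do not support them:

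- A reader might infer that a null app would be declared effective in about 40% of trials. Efficacy is judged on the intention-to-treat ANCOVA at the 5% level. The 40% is the chance that one sensitivity p-value falls below 0.05 under one set of assumptions.
- A reader might infer that the bias must favour the app. No direction is given. Less strained workers may use it more, or those with most need may.
- A reader might infer from "Only the amount of Dailys will be recorded for each participant" that weekly use cannot be computed. That sentence directly follows a privacy statement about photos and notes, and elsewhere the protocol says frequency of use will be tracked. What remains is an unreconciled definition of use.

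**Conclusion.** The concern holds, at moderate severity. The empty control group follows from the text alone. That the users-versus-all-controls comparison is unprotected by randomisation follows from the design and needs no numerical assumption.

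The size is conditional: a spurious difference of 0.06-0.35 SD in magnitude, and a rejection rate of roughly 12-92% for this sensitivity test under a true null. Both rest on the assumed adherence of 30-70% and the assumed gap of 0.2-0.5 SD. The documents supply neither figure.

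The primary ANCOVA, N = 788 and the other two sensitivity analyses are unaffected.

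**What to change.** 1. Replace the per-protocol comparison with a complier-average causal effect. Use two-stage least squares on all randomised participants, with arm as instrument and T1 rumination as covariate. Controls count as non-adherent by design.
2. Repeat it with adherence defined as any Daily completed. The method assumes that assignment has no effect on participants below the threshold. That is doubtful at three uses per week, because lighter users still complete some Dailys and receive prompts and feedback.
3. If frequent users against all controls is also reported, label it non-randomised and supportive, and do not present it as a check of robustness.
4. Define one use from the recorded variable by reconciling the count of Dailys with the statement that frequency of use is tracked. State the weeks over which use is counted. The start of intervention access must be reconciled too, since the abstract gives two weeks before vacation and the intervention section three.

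**Cost.** Wording and a few lines of code, on data already collected. The interval is wider: the intention-to-treat SE is √(2/394) = 0.0712, so at 50% adherence the complier SE is about 0.0712/0.5 = 0.142, against 0.0873 for the naive comparison. The complier effect is essentially the intention-to-treat effect divided by adherence (0.20/0.5 = 0.40 at the design effect). It therefore answers a question about adherers and does not independently test the primary result. Robustness should rest on the other sensitivity analyses.

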#### Sample size calculation

Sample size calculation was based on the expected standardized difference in the primary outcome measure — work-related rumination (Irritation Scale, [76]) — between the intervention and control groups 2 weeks post vacation. Evidence from meta-analyses and systematic reviews on the efficacy of digital interventions for mental health, and specifically stress management, in workers indicate an effect size of ﻿*g* = 0.54 [77]. More precisely, data on mental health apps as a standalone treatment for clinical samples targeting various conditions yield mixed results: for instance, a significant effect for depression ﻿*g* = 0.33, but no effect for ﻿anxiety [70]. Few RCTs indicate the potential of any app-based intervention targeting stress-related complaints amongst workers [65, 66, 74]. Though clear results concerning the efficacy of app-based interventions cannot be drawn, findings nonetheless indicate their potential. From a public health perspective, the aim is to reach the whole population. As such, smaller effects are meaningful, as more people can potentially benefit from an intervention. Taking these two lines of reasoning together, we regard an effect of *d =* 0.20 for work-related rumination as meaningful, especially when considering that the app constitutes a low-intensity self-help intervention for the general working population. A priori G*Power analysis [78] for a two-tailed test, in which 80% power and a 5% significance level are assumed, indicates that an overall sample size of *N* = 788 is needed to detect differences statistically.

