Third, findings from previous observational studies suggest that the beneficial vacation effect experienced by workers is not sustained, but fades out shortly after they return to work, with mental health indicators returning to pre-vacation levels [46, 47, 56]. Consistent with previous investigators, who usually selected 2 weeks to describe the fading effect, we maintained this timeframe for our primary measurement. Additionally, a 2 week extended follow-up also is included, albeit only to assess stabilisation after the vacation in the intervention group. Further investigations are, therefore, needed. While 2 weeks may be insufficient to verify lasting behavioural changes, they might provide insights into whether the fadeout effect can be reduced. If Holidaily appears to be effective in the short-term only, future studies should also consider potential facilitators and barriers for long-term maintenance.

In the present study, three possible barriers might limit the intervention’s effect to two-weeks. For instance, after their vacation, workers may experience reduced motivation and increased effort to engage in recovery behaviours, due to stresses encountered at work (e.g., work accumulation during their absence; see also [57]). This might lead to an initial relapse, prompting the fading of the beneficial effect. To overcome such barriers, certain behavioural change techniques, like prompts and self-monitoring, were integrated into this intervention to promote engagement in recovery behaviours during daily working life. It is unclear whether these are appropriate strategies, however. To assess changes and control for potential confounders, for instance, workers’ motivation/engagement is being measured by the Utrecht Work Engagement Scale [95]

Second, the length of workers’ vacation may play a greater role determining the maintenance of behavioural change than previously anticipated. In one study, as few as 18 or as many as 254 days are required before a newly adopted health behaviour — like improved diet or regular exercise — becomes stable and replaces previously dominant behaviours [126]. Contrastingly, workers in Germany are legally entitled to a minimum of 24 days of paid vacation. Although the length of workers’ vacation period may be long enough to initiate short-term behavioural change, it might be insufficient for benefits to be maintained long-term. Hence, vacation length will be considered as a confounder.

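### The covariate sensitivity analysis selects variables by chance imbalance rather than prognosis, and the reported Cohen's d leaves out the baseline adjustment used in the test it accompanies

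*Protocol article*

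**What the plan says.** Three sections of the protocol article bear on this point.

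- **Sensitivity analyses.** After a completer and a per-protocol analysis, the third check deals with baseline imbalance: "to account for potential baseline differences, despite randomisation, we will include all continuous variables with a between group difference of" a stated size, namely a d of at least 0.20. Categorical variables enter at a difference of 10% or more. The candidate variables are not listed, and no relation to the outcome is required.
- **Primary analysis.** The test is an ANCOVA of work-related rumination two weeks after vacation, with the baseline score of the same measure as covariate. The article justifies ANCOVA by its protection against bias and its gain in precision.
- **Statistical analyses.** The effect size is Cohen's d, to be given for every continuous outcome, primary or secondary. The article states that it "will be calculated based on group differences in means post-vacation, standardized by the pooled standard deviation of the post-vacation scores". On its plain reading this contains no baseline term.

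The planning value is in Sample size calculation: "we regard an effect of *d =* 0.20 for work-related rumination as meaningful", which leads to a total of 788.

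**The concern.** Under Procedures, the baseline questionnaire is completed before randomisation, so any baseline difference between the arms is due to chance. How far such a difference moves the estimated effect depends on two things: its size, and how strongly the variable predicts the outcome. The rule looks only at the first. A difference of 0.19 SD in a strong predictor is ignored, while 0.21 SD in an irrelevant variable brings that variable into the model. A robustness check built this way mostly reproduces the primary model, and when it does not, the added covariate has been chosen by chance.

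The effect size raises a separate question of consistency. The plan prefers a baseline-adjusted analysis for the test, then defines the accompanying effect size without the adjustment. The p value and the effect size in the same results row would come from two different estimates, and the less precise one would be the figure readers carry away.

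**Working it through.** **Inputs from the article.** Total 788, 1:1 allocation, so 394 per arm. Target d = 0.20, two-sided 5% level, 80% power ("for a two-tailed test, in which 80% power and a 5% significance level are assumed"). Thresholds: d of 0.20, or 10%, read here as percentage points.

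**Assumptions, because the article gives no figure.**
- Candidate variables: about 30 scales or subscales measured at T1 besides the primary outcome (Table 1), plus about 6 continuous items from the Demographics section. That makes about 36 continuous variables, with about 5 categorical ones.
- Correlation r between baseline and two-week rumination: 0.3 to 0.7.

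**1. The plan's own figure.** The exact two-sample t calculation gives 394 per arm, 788 in total, with power 0.8006. The normal approximation gives 393 per arm. The stated 788 is reproduced.

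**2. Chance that one continuous variable triggers.**
- SE(d) = sqrt(2/394) = 0.0712.
- 0.20/0.0712 = 2.81, so the two-sided probability is 0.0050 (0.0051 with the t distribution).
- For a two-level categorical variable, the exact binomial probability of a 10-point difference is 0.49% at 50% prevalence, 0.21% at 30% and 0.04% at 20%.

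**3. Chance that the rule triggers at all.** With k independent continuous variables this is 1 - (1 - 0.0051)^k.

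| Continuous candidates | At least one triggers | None triggers |
|---|---|---|
| 30, independent | 14% | 86% |
| 36, independent | 17% | 83% |
| 36, inter-correlation 0.3 (simulated) | 13% | 87% |
| 36, inter-correlation 0.5 (simulated) | 10% | 90% |

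The expected number triggered among 36 is 36 x 0.0051 = 0.18. Five two-level categorical variables would add at most about 5 x 0.49% = 2.4 percentage points. If recruitment falls short, the per-variable chance rises to 1.4% at 300 per arm, 4.6% at 200 and 15.7% at 100. Selection is then more frequent but still blind to prognosis.

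**4. Raw against adjusted d.** With equal SDs at both times and complete data:
- SE of raw d = 0.0712.
- SE of adjusted d = 0.0712 x sqrt(1 - r^2).
- Raw minus adjusted d is r times the chance baseline difference, so its SD is r x 0.0712 and its 95% range is ±1.96 x r x 0.0712.

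| r (assumed) | SE raw | SE adjusted | 95% range of raw minus adjusted | Share of 0.20 |
|---|---|---|---|---|
| 0.3 | 0.071 | 0.068 | ±0.042 | 21% |
| 0.5 | 0.071 | 0.062 | ±0.070 | 35% |
| 0.7 | 0.071 | 0.051 | ±0.098 | 49% |

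For example, at r = 0.5 a baseline difference of 0.10 SD moves raw d by 0.5 x 0.10 = 0.05, a quarter of the target.

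**The case against.** The case for leaving the plan alone has real force. The rule governs one of three sensitivity analyses. It is stated in advance with numeric thresholds and uses baseline data, so it gives no room for choices driven by outcomes. The primary model already contains the obvious prognostic covariate, and the secondary ANCOVAs adjust for their own baselines. If no material imbalance appears, there is arguably nothing to account for. Raw d is unbiased under randomisation and conventional, and matches the unadjusted difference used for planning. All of this stands, and it limits the weight of the point. It does not answer the objection that size of imbalance without prognosis is the wrong criterion, or that the test and the effect size use different estimates.

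Four stronger readings are tempting, but the article does not support them.

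- A reader might infer that the rule will practically never act. That is true for each variable, but over the whole list it acts in roughly 10% to 17% of trials.
- A reader might infer that power is being lost. The primary ANCOVA already takes the gain from baseline rumination: at an assumed r = 0.5 its power for d = 0.20 is 90.0%. The article gives nothing from which to size a further gain. Its Mental detachment section reports strong overlap between detachment and rumination, so a detachment covariate could add little.
- The Limitations section says "vacation length will be considered as a confounder" and introduces work engagement with "To assess changes and control for potential confounders, for instance". A reader might infer that these adjustments have been forgotten. The model for them is detail an article may leave to the analysis plan, and both variables can be obtained at T1.
- Because engagement is also measured after randomisation, a reader might fear adjustment for later values. Nothing in the article says that later values enter a model, and the sensitivity rule concerns baseline differences.

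**Conclusion.** The point holds as an improvement to one sensitivity analysis and to the reported effect size. It is not a flaw in the primary test, whose p value is unaffected, and no gain in power is claimed.

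At the planned size, the covariate check repeats the primary ANCOVA in roughly 83% to 90% of trials and otherwise adds a variable selected by chance. This rests on full recruitment and on an assumed count of about 30 to 36 continuous candidates. Raw d is less precise than the adjusted estimate, and the two can differ by about ±0.04 to ±0.10 (95%) against a target of 0.20. This rests on an assumed r of 0.3 to 0.7. At the low end of that range the loss of precision is small (0.071 against 0.068); at the high end the possible disagreement is about half the target effect.

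**What to change.** Two changes of wording:

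1. **Sensitivity analyses.** Replace the imbalance rule with a short list of prognostic variables, fixed before unblinding and measured at T1, added to baseline rumination. Examples are WRRQ affective rumination, time pressure, work engagement and planned vacation length. The article gives no evidence on their prognostic value, so the trial team should justify the final choice from subject knowledge.
2. **Statistical analyses.** Define Cohen's d, with its 95% CI, as the ANCOVA-adjusted mean difference divided by the pooled SD of the post-vacation scores. Keeping that SD preserves the scale of the planning value; only the numerator changes. Raw d can be reported alongside if wanted.

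The cost is wording only. The example covariates are in Table 1 at T1, or follow from the vacation dates collected in the T1 demographics questionnaire, so no new data, participants or time are needed.
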